## Discussion

This protocol describes a large (*n* = 500) randomised controlled trial examining the effects on depression of internet-administered behavioural activation and physical exercise programs, with relapse prevention and treatment rationale as additional distinguishable components. As the economic strain and personal suffering associated with depression continues to increase, so does the need for a variety of treatment methods. Despite their potentials as low-threshold, low-cost, high-flexibility treatments of depression, behavioural activation and physical exercise have yet to be the subject of much research. Any future integration of behavioural activation and physical exercise into healthcare systems will of course require scientific evidence of the effects of these treatments. The study herein described will make substantial contributions to the body of knowledge on these areas, while also examining the separate effects of providing a clear treatment rationale. The potential of a CBT-style program to prevent depression relapse will also be examined. The randomised controlled design is stringent throughout the study, allowing valid conclusions on the effects of the respective interventions. To our best knowledge, this study is also the first to feature Internet-administered behavioural activation; the results will consequently provide a first indication whether the treatment can be adequately translated to this promising administration format.

This study has some limitations that need to be recognised. For ethical reasons, individuals suffering from too severe depression, with or without the risk of suicide, will not be included. Since the participants in the waiting list control group will receive treatment after a 12-week delay, this study will lack a control group in the follow-up period. This again is for ethical reasons. As in almost all studies featuring psychotherapeutic interventions, blinding participants and researchers is not feasible. A final aspect in need of recognition is the involvement of the master’s students in clinical psychology. To compensate for the students’ lack of training and experience, an experienced licensed clinical psychologist and psychotherapist will supervise all involvement.

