**Methods/Design:**

This randomised controlled trial will include 500 participants meeting the diagnostic criteria for major depression, recruited in multiple cycles and randomised to either a waiting list control group with delayed treatment, or one of the four treatment groups: (1) physical exercise without a clear treatment rationale; (2) physical exercise with treatment rationale; (3) behavioural activation with treatment rationale; or (4) behavioural activation without a clear treatment rationale. Post treatment, half of the participants will be offered a relapse prevention program. Primary outcome measure will be the Patient Health Questionnaire 9-item. Secondary measures include diagnostic criteria for depression, as well as self-reported anxiety, physical activity and quality of life. Measurements - done via telephone and the Internet - will be collected pre-treatment, weekly during treatment period, immediately post treatment and then monthly during a 24-month follow-up period.

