Initial selection of participants will be based on the results of the online screening instruments, consisting of MADRS-S, PHQ-9 [20], IPAQ [21], QOLI [22], GAD-7 [23] (see below) and a number of additional questions on demographics and previous treatment experiences. While the other instruments return as outcome measures (see below), MADRS-S will only be used in the screening procedure as a measure of the severity of depression symptoms. Previous research has shown that MADRS-S has a good internal consistency (Cronbach’s alpha 0.85 to 0.94), a satisfactory singe-component factor structure (47% to 69% variability explanation power), and a good correlation (Pearson’s correlation 0.81 to 0.91) with the clinician-rated version [24]. The psychometric properties of the Internet-administered version of MADRS-S has found to be sufficiently similar to the pen and paper version [25,26].

Prospective participants meeting initial inclusion criteria will be interviewed via telephone according to the Mini-International Neuropsychiatric Interview (MINI) [27] manual. Diagnostic interviews conducted per telephone have previously been found to be in very good agreement with face-to-face interviews regarding major depressive disorder [28]. The screening interviews will be conducted by supervised, clinical psychology master’s students, trained in the use of MINI. The interviewers will meet together with experienced clinical psychologists and psychiatrists to discuss final inclusion and to tailor the respective treatment program to each participant. Randomisation of participants to the different groups will be done by a statistician not otherwise involved in the study, using a computer-generated list with variables not known to the principle researchers. Participants who drop out will not be replaced.

Participants will access treatment programs, register data and communicate with their therapists using an SSL-encrypted online interface. Participants will log in using their anonymous participant number, a chosen password and unique, single-use codes sent by SMS or ordinary mail.

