### Interventions

All interventions will be administered and monitored via the online interface. Both the BA and physical exercise groups will receive therapist support, provided by the above-mentioned clinical psychology master’s students, supervised by an experienced clinical psychologist.

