#### Diagnosis

Initial diagnosis of depression, according to DSM-IV criteria, will be made using part A of the structured Mini-International Neuropsychiatric Interview (MINI) [27]. Additionally, each follow-up month, 33% of each treatment group will be interviewed per telephone. Hence, on an individual level, interviews will be conducted every third month during the follow-up period of 24 months (namely, eight follow-up interviews in total for each participant). On a group level, interviews will be conducted every month. The built-in data-loss of 66% each month will however be data missing completely at random since the participants are randomised to their respective months, making the procedure unbiased (see [33]).

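### The statement that researchers cannot be blinded is too broad: it does not apply to the telephone interviewers who make the follow-up depression diagnosis, and nothing stated keeps a therapist from rating a participant they treated

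*Protocol article*

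**What the plan says.** All references are to the protocol article.

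- **Discussion, limitations paragraph.** By analogy with most psychotherapy trials, it says that "blinding participants and researchers is not feasible". Outcome assessors are not considered separately.
- **Screening and participants.** "The screening interviews will be conducted by supervised, clinical psychology master’s students, trained in the use of MINI". The same interviewers meet senior clinicians to decide on inclusion and to tailor each participant's programme.
- **Interventions.** Therapist support in both the behavioural activation and the exercise groups is "provided by the above-mentioned clinical psychology master’s students, supervised by an experienced clinical psychologist".
- **Diagnosis.** After the initial MINI, "each follow-up month, 33% of each treatment group will be interviewed per telephone", which gives "eight follow-up interviews in total for each participant". No interviewer is named and masking is not mentioned. The section calls the scheme unbiased, but the reason given is the random allocation of participants to interview months, which concerns missing data and not rating.
- **Abstract, Methods/Design.** "Secondary measures include diagnostic criteria for depression". The Secondary outcomes section, by contrast, counts three measures (IPAQ, GAD-7, QOLI), and the diagnosis is not one of them.

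**The concern.** The reason blinding fails in psychotherapy trials is that the participant knows what they receive and the therapist knows what they deliver. A telephone interviewer does neither and need not know the arm. Treating all researchers alike therefore gives up a protection that is available.

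The interview diagnosis is the only depression outcome described that is rated by someone other than the participant. If the rater knows the allocation, and in particular if the rater was the participant's therapist, expectation can enter the rating of borderline symptoms. A consistent shift of this kind does not average out over repeated interviews: pooling eight interviews narrows the standard error but leaves the bias where it was.

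**Working it through.** No figure in the document is in dispute. The check is one of reading, followed by a sense of scale.

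**1. Who interviews and who treats.** Screening and participants gives the screening interviews to the master's students. Interventions gives therapist support to those same students. They are one pool. Diagnosis leaves the follow-up interviewer open, and the students are the only interviewers named anywhere. Overlap at follow-up is therefore an inference; overlap at screening is stated, but at that point no arm has been assigned.

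**2. Volume.** 24 months / 3 = 8 interviews per participant, as the article states. At most 8 × 500 = 4,000 ratings. This is a count and not a measure of bias.

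**3. Which contrast is exposed.** The waiting list is dissolved after 12 weeks, so the follow-up interviews support no comparison with untreated controls. The arms with and without rationale, within each type of treatment, receive equal therapist support, so a consistent direction of rater expectation is less plausible there. It is most plausible for relapse prevention against none. The sample size paragraph in Screening and participants gives 250 receiving relapse prevention, leaving 500 − 250 = 250 without.

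**4. Precision for one interview per participant, no drop-out, proportion 50%.** SE = √(2 × 0.25 / n).
- 250 v 250: √(0.5 / 250) = 0.0447, about 4.5 points.
- 125 v 125 (two single arms): √(0.5 / 125) = 0.0632, about 6.3 points.

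**5. Assumed rater shift of 5 to 10 points** (the documents give none).
- 250 v 250: 5 / 4.5 = 1.1 to 10 / 4.5 = 2.2 SE.
- 125 v 125: 5 / 6.3 = 0.8 to 10 / 6.3 = 1.6 SE.

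**6. Illustration as a false-positive rate.** Assume a true depression rate of 30% in both relapse-prevention halves, 250 v 250, one interview, a two-sided 5% test, and a diagnosis under-called in one half by a relative amount b. With p₁ = 0.30, p₂ = 0.30(1 − b) and p̄ their mean,

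P = Φ[(p₁ − p₂ − 1.96·SE₀) / SE₁], where SE₀ = √(2p̄(1 − p̄)/250) and SE₁ = √((p₁(1 − p₁) + p₂(1 − p₂))/250).

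| b | Recorded rate in that half | Chance of a significant result in that direction |
|---|---|---|
| 0 | 30.0% | 2.5% |
| 5% | 28.5% | 5.6% |
| 10% | 27.0% | 11.2% |
| 15% | 25.5% | 20.1% |
| 20% | 24.0% | 32.6% |

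The 30% rate and the values of b are assumptions. The table shows sensitivity and does not estimate the bias in this trial.

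**The case against.** The strongest reply is that who makes the follow-up calls, and whether they are masked, is operational detail that a journal article may leave to the full protocol, and that the Discussion already discloses the lack of blinding as a limitation. The first half would stand if the article were merely silent. It is not: it says that researchers cannot be blinded, and the reason it offers does not reach interviewers. Disclosure does not repair a reason that does not apply.

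Several stronger readings are tempting, and the document does not support them.

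- **That therapists will conduct the follow-up interviews.** A reader might infer this from the shared pool, but the overlap is documented only for screening.
- **That interviewers can see the arm in the online interface.** Staff access is not described.
- **That the interview diagnosis feeds the Kaplan-Meier analysis.** The Analysis section defines no event, and the monthly PHQ-9, which the article says can also serve diagnostically, is an equally possible source.
- **That an unblinded interview is worthless, or that a masked one would guard against reporting bias.** The interview still rests on what an unblinded participant says. Masking the interviewer addresses rating bias only.
- **That a rota would remove the bias.** Participants can reveal their programme, so it would only reduce it.

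The standing of the diagnosis is also less settled than the abstract suggests, given the three measures counted under Secondary outcomes. That limits the weight of the point but does not answer it.

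**Conclusion.** The point holds in a limited form. The infeasibility statement is right for participants and therapists and too broad for telephone interviewers. With a shared student pool and no named follow-up interviewer, the interview diagnosis has no stated protection from rater bias. That a student could rate a participant they treated is an inference from silence and not a stated plan.

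The consequence is confined to the interview diagnosis and any analysis built on it, chiefly relapse prevention against none. There the standard error is about 4.5 points (one interview each, 50%, no drop-out), so a rater shift of a few points would not be negligible. Whether such a shift would occur, and how large it would be, cannot be known from the document. The PHQ-9 is entered online by participants and no interviewer rates it, so the primary analysis and the sample size are untouched. This is a cheap improvement and not a flaw in the trial's main conclusion.

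**What to change.** - State that each follow-up interview is done by one of the existing students who did not support that participant and who is masked to arm and to relapse-prevention status.
- Ask participants at the start of the call not to mention their programme.
- In the Discussion, confine the infeasibility statement to participants and therapists.
- If masking is not adopted, report the interview diagnosis as unblinded.

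The cost is scheduling among existing students and control of who can see allocation; no extra interviews are needed. Some accidental unblinding will remain.

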## Trial status

Recruitment is scheduled to begin in January 2013. The participants of the first recruitment cycle are planned to commence treatment later that spring.

## Abbreviations

BA: Behavioural activation; CBT: Cognitive behavioural therapy; DSM-IV-TR: Diagnostic and statistical manual of mental disorders, fourth text-revised edition; GAD-7: Generalized Anxiety Disorder 7; IPAQ: International Physical Activity Questionnaire; MADRS-S: Montgomery-Åsberg Depression Rating Scale Self-rated; MINI: Mini-International Neuropsychiatric Interview; PHQ-9: Patient Health Questionnaire 9; RP: Relapse prevention program; QOLI: Quality Of Life Inventory; TCS: Treatment Credibility Scale; TICP-P: Trimbos/iMTA questionnaire for Costs associated with Psychiatric illness.
